***STUDY PROTOCOL***

**Research Method**

The current study is a semi-experimental study in which the effect of the independent variable (use of media in patient education) on the dependent variable (satisfaction of patients undergoing colonoscopy) will be investigated.

**Type of Research**

The current research is semi-experimental and includes the implementation of media intervention in the education of colonoscopy patients referred to Ayatollah Taleghani Medical Education Center.

**Research Sample**

The statistical population of the present study will include colonoscopy patients referred to Ayatollah Taleghani Medical Education Center and the research sample will be patients with inclusion criteria.

**Adult sample size**

The number of samples is obtained using the following relationship in each group:

$$n\geq2\frac{\left( z_{\alpha/2}+z_{\beta} \right)^{2} \sigma^{2}}{(\mu_{1}- \mu_{2})}$$

where the probability of type 1 error:

$$\alpha=0.05 \to z_{\alpha/2}=1.96$$

Probability of type II error:

$$\beta=0.10 \to z_{\beta}=1.28$$

$$1- \beta=0.90$$

Power of observed effect size:

$$\left( \mu_{1}- \mu_{2} \right)/{\sigma=0.75}$$

${\mu_{2},\mu}_{1}$indicate the average satisfaction score of the adults.

Minimum sample required:

$$n=2\left( 1.96+1.28 \right)^{2} \left( \frac{1}{0.75} \right)^{2} =37$$

At least 37 adults in each group should be considered for the research, and considering 40% attrition, the number of samples is 50 patients in each group.

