**data analysis method**

Analyzing the research data using statistical package software for social sciences version 20, and using descriptive tests such as mean, variance, and standard deviation, and using inferential tests such as chi-square, independent t-test, and analysis of variance, the data will be analyzed. The Smirnov Kolmograph test will be used to check the normality of the data. To compare the two groups, chi-square, Menio-Whitney and independent t-tests will be used, and to compare the results in the intervention and control groups, independent t-test or Menio-Whitney statistical tests will be used. In all tests, a significance level of less than 0.05 will be considered.

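### Fifty patients per group do not cover the stated 40% attrition; at that attrition the stated 90% power falls to about 82%

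*Protocol*

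**What the plan says.** Under the heading on adult sample size, the protocol uses the usual formula for comparing two means, with two-sided α = 0.05 (z = 1.96), β = 0.10 (z = 1.28, so 90% power) and a standardised difference of 0.75 in mean satisfaction score. The result is that "At least 37 adults in each group should be considered for the research". The same sentence then allows for losses: "considering 40% attrition, the number of samples is 50 patients in each group".

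The protocol gives no inflation formula, no basis for the 40%, and no other attrition figure. The data analysis section says that, to compare the results of the intervention and control groups, "independent t-test or Menio-Whitney statistical tests will be used".

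**The concern.** An attrition allowance is meant to leave the required number of evaluable patients after the expected losses. Here the number left is smaller than the number the plan has just said it needs. So the stated power (90%), the attrition allowance (40%) and the enrolment (50 per group) contradict one another.

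This section is the only place where the protocol quantifies what the study can detect. If losses came near 40% and the comparison was not significant, a reader would take it as a null result from a study with 90% power that had already allowed for those losses. The true chance of missing a 0.75 SD difference would be about 17% to 18%, not 10%.

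**Working it through.** **Inputs, all from the sample size section:** z(α/2) = 1.96; z(β) = 1.28; standardised difference d = 0.75; minimum 37 per group; attrition 40%; enrolment 50 per group, equal groups.

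**1. The plan's base figure.** n = 2(1.96 + 1.28)² / 0.75² = 2 × 10.4976 / 0.5625 = 37.32. The stated 37 is reproduced by rounding down. Because the formula is written as n ≥, the smallest whole number that satisfies it is 38.

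**2. The attrition step.** To keep n evaluable after a proportion a is lost, enrol n/(1 − a).
- From 37: 37/0.60 = 61.7, so 62 per group.
- From 38: 38/0.60 = 63.3, so 64 per group.

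The stated 50 is not reproduced. It is 12 per group (24 in total) short of 62.

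**3. Other routes to 50.**
- Adding 40% on, which does not protect power: 37 × 1.40 = 51.8, so 52. This is close to 50 but still above it.
- A one-sided test: the base is 31, and 31/0.60 = 51.7, so 52. The plan's use of z(α/2) = 1.96 rules this out in any case.
- The attrition that 50 can absorb: 1 − 37/50 = 26%, or 1 − 38/50 = 24%.

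**4. What remains at 40% attrition.** 50 × 0.60 = 30 per group.

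**5. Power at d = 0.75, two-sided 5%.** The normal approximation is Φ(d√(n/2) − 1.96). At n = 30 this is Φ(0.75 × √15 − 1.96) = Φ(0.945) = 0.828. The t-test column uses the noncentral t distribution.

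| Evaluable per group | Normal approximation | t-test |
|---|---|---|
| 30 | 82.8% | 81.5% |
| 37 | 89.7% | 88.9% |
| 38 | 90.5% | 89.7% |
| 39 | – | 90.5% |
| 50 (no loss) | 96.3% | 96.0% |

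**6. Difference detectable with 90% power at 30 per group.** Normal approximation: 3.24 × √(2/30) = 0.84 SD. t-test: 0.85 SD. The plan states 0.75 SD.

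**7. The printed formula.** As it reads in the text, the general relationship divides by (μ1 − μ2) without a square, whereas the worked line squares 1/0.75. If σ is set to 1 (an assumption; the protocol gives no σ), the unsquared form gives 2 × 10.4976 / 0.75 = 28.0. The figure of 37 comes from the squared form and is not affected.

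**The case against.** The strongest reply is that the effect is conditional and moderate. With no losses, 50 per group gives 96% power, and about 90% is kept up to 24% to 26% attrition. The 40% is a planning allowance with no stated basis, and actual losses may be much lower. Power of about 82% would be acceptable to many, and no test, significance level or hypothesis changes. All of this is true, and it limits the consequence. It does not reconcile the figures: the plan chose 40% and 90%, and its enrolment does not deliver both.

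Three narrower objections also stand.
- **Basis of the power figures.** The normal approximation and the t-test differ by about one percentage point and should not be mixed. Like for like, from 37 to 30 evaluable, the type II error goes from about 10% to 17.2% (normal) or from 11.1% to 18.5% (t-test).
- **Origin of the error.** Adding 40% on instead of dividing by 0.60 is a plausible source of the 50, but 37 × 1.35 = 49.95 fits more closely, and a mistyped percentage is possible. Only the mismatch is established.
- **The two smaller slips.** Rounding down costs about 0.3 percentage points of power (89.7% against 90%). The missing square may be a typing slip or a loss in converting the equation. Both are editorial.

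**Conclusion.** The concern holds. A minimum of 37, 40% attrition and 50 enrolled per group are mutually inconsistent, and nothing elsewhere in the protocol reconciles them. At the plan's own attrition, 30 per group remain. Power is then 81.5% to 82.8% instead of 90%, and the difference detectable with 90% power is 0.84 to 0.85 SD instead of 0.75 SD.

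These figures assume equal loss in the two groups, no outcome data from lost patients, the plan's standardised difference of 0.75, and a comparison of means. Power for the Mann-Whitney alternative was not computed. The statement is wrong as written and should be corrected, although the loss of power appears only if attrition exceeds about 24% to 26%.

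**What to change.** Restate the figures on one named basis. Using the plan's own normal approximation, suitable wording would be:

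> With 50 patients per group, the study has 90% power to detect a standardised difference of 0.75 (two-sided 5%, normal approximation) with up to 24% attrition (38 evaluable per group). If 40% are lost, 30 per group remain, power is about 83%, and 90% power is reached only for differences of at least 0.84 SD.

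If the t-test is the chosen basis, the corresponding figures are up to 22% attrition (39 evaluable; 1 − 39/50 = 0.22), power of 81.5% at 40% loss, and 0.85 SD.

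In the same edit, round 37.3 up to 38 and check that the printed formula has the square on (μ1 − μ2).

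This costs protocol wording only and no extra patients. The price is a less favourable statement of attrition tolerance or power. If the sponsor expects 40% loss and wants to keep 90% power, enrolment has to rise to 62 per group (64 from a base of 38). Alternatively, the sponsor can justify a lower attrition figure. That choice is the sponsor's, but the three stated figures must agree.

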**Sampling**

In this research, sampling will be done by available method and the participants will be selected purposefully in two control and intervention groups. The similarity of the two groups in terms of age, sex, education level, disease, background and cause of hospitalization will be statistically investigated.

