**Data collection method**

In the present study, data will be collected by completing a questionnaire. In this way, after obtaining the code of ethics from the ethics committee and the letter of introduction from Shahid Beheshti University of Medical Sciences and Health Services, the researcher explains the goals and working methods to them through coordination with the officials of the Ayatollah Taleghani Medical Education Center and will conduct the study.

In order to collect data from the patients, first a written consent to participate in the research will be obtained from them, after explaining the objectives and the method of doing the work to participate in the research. Both groups complete the demographic questionnaire (Appendix 1) and the colonoscopy satisfaction questionnaire (Appendix No. 2) (colonoscopy) and the results are compared in the two control and intervention groups.

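### The protocol gives no non-discretionary rule for placing patients in the media or control group, and its similarity check cannot make up for that

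*Protocol*

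**What the plan says.** The Research Method section declares a non-randomised design and an effect as its aim: "The current study is a semi-experimental study in which the effect of the independent variable" of media education on satisfaction is to be investigated.

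The Sampling section forms the groups in one sentence: "sampling will be done by available method and the participants will be selected purposefully in two control and intervention groups". The next sentence gives the one safeguard: "The similarity of the two groups in terms of age, sex, education level, disease, background and cause of hospitalization will be statistically investigated".

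The Data collection method section goes from consent to the two questionnaires and then says that "the results are compared in the two control and intervention groups". It describes no assignment step and no baseline satisfaction score. For the group comparison, the data analysis section says that "to compare the results in the intervention and control groups, independent t-test or Menio-Whitney statistical tests will be used". Analysis of variance is also listed there, without a stated purpose.

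The Adult sample size section arrives at 37 per group from a standardised difference of 0.75, raised to 50 per group.

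**The concern.** A comparison of two groups estimates the effect of the media only if the groups would have had similar satisfaction without it. If whoever recruits can decide which patient goes where, this cannot be assumed. Patients who seem motivated, calm or cooperative could end up more often in one group. The outcome in Appendix No. 2 is self-reported and asks, for example, about feeling ready and about overall satisfaction, so it is the kind of measure on which such patients may answer differently.

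Any difference already present between the groups is added to the media effect and tested with it. A larger sample does not remove it; it only makes the pre-existing difference more likely to reach significance. The problem cannot be repaired once patients are enrolled, because factors that were never recorded cannot be adjusted for.

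**Working it through.** **1. The plan's own figure.** Inputs from Adult sample size: z = 1.96 and 1.28, standardised difference 0.75.

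n = 2 × (1.96 + 1.28)² / 0.75² = 2 × 10.4976 / 0.5625 = 37.3 per group

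The stated 37 is reproduced (38 if rounded up). Reading the 0.75 SD as an effect of the media presumes groups that are otherwise comparable.

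**2. Is there an assignment rule elsewhere?** Research Method and Type of Research name the design. Research Sample and the inclusion and exclusion criteria define who is eligible. Data collection method covers consent and questionnaires. None of them says how an eligible patient comes to be in one group and not the other. The sentence in Sampling stands alone.

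**3. What a selection difference would do.** Let b be a pre-existing difference in satisfaction, in SD units, with no true media effect. The documents give no value for b, so it is an **assumption** and is varied. With SE = √(2/n) and a two-sided 0.05 level:

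P(p < 0.05) = Φ(b/SE − 1.96) + Φ(−b/SE − 1.96)

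At n = 50, SE = √(2/50) = 0.200. For b = 0.3: Φ(1.5 − 1.96) + Φ(−1.5 − 1.96) = 0.323.
At n = 37, SE = √(2/37) = 0.2325. For b = 0.3: Φ(1.29 − 1.96) + Φ(−1.29 − 1.96) = 0.252.

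| Assumed b (SD) | 50 per group | 37 per group |
|---|---|---|
| 0 | 5.0% | 5.0% |
| 0.1 | 7.9% | 7.1% |
| 0.2 | 17.0% | 13.8% |
| 0.3 | 32.3% | 25.2% |
| 0.5 | 70.5% | 57.6% |

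Using the t distribution changes the rows for 0.2 and 0.3 by at most half a percentage point (16.8% and 31.8% at 50; 13.6% and 24.7% at 37). Set against the planned effect, 0.2/0.75 = 27% and 0.3/0.75 = 40%.

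**4. What the similarity check can see.** With 50 per group and a test at 0.05:

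| Imbalance between groups | Power to detect it |
|---|---|
| 50% v 60% | 17% |
| 50% v 65% | 33% |
| 50% v 70% | 53% |
| 0.3 SD in a continuous factor | about 32% |

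The last row uses the formula in step 3, and the others use the normal approximation for two proportions. A non-significant check is therefore the likely result even when a moderate imbalance is present. It would not show that the groups are alike.

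**The case against.** **The design is declared.** The protocol calls itself semi-experimental twice, and such studies do set out to estimate effects. This stands: the lack of randomisation is disclosed, and the aim alone is not a contradiction. But a semi-experimental design does not require discretionary assignment, and disclosure does not remove confounding.

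**The wording may be milder than it looks.** The text appears to be a translation, and the sentence sits under Sampling. It could mean only that available patients who meet the criteria are recruited. This also stands. On that reading the defect is a missing assignment rule, not hand-picking, and discretion remains open either way.

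**A reader might infer that the researcher picks each patient knowing which group is being filled.** The documents do not say who selects, when, or with what knowledge. That reading should not be presented as fact.

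**A reader might infer that nothing in the design addresses selection.** That goes too far. The similarity check exists and includes education, and the inclusion criteria require every patient to have access to virtual space and educational videos, which narrows differences in media access. What remains are unlisted factors such as motivation or anxiety, the low power shown above, and the absence of any stated consequence if an imbalance is found.

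**Adjustment may be planned elsewhere.** A statistical analysis plan may exist and is not at hand, and analysis of variance is listed. The lack of a named covariate model therefore carries no weight here. Adjustment could in any case reach only what is measured.

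**Conclusion.** The point holds in a limited form. As written, the protocol leaves assignment to discretion, and its only safeguard does not secure comparable groups. Following it can confound who was selected with the effect that the study sets out to investigate.

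The figures of 17% to 32% (50 per group) and 14% to 25% (37 per group) are a sensitivity range. They rest on an assumed selection difference of 0.2 to 0.3 SD, no true effect, equal variances and equal groups. They show what such a bias would do, not that one of that size or direction exists. It would be tempting to conclude that the 5% error rate is certainly invalid; the documents do not support so firm a statement, because they give no estimate of the bias. The power of the similarity check depends on no assumption about bias in the outcome, only on the size of the imbalance to be found.

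**What to change.** Replace the group-formation sentence under Sampling before enrolment starts, with wording such as:

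> Consecutive eligible patients are approached. After written consent and completion of the demographic questionnaire, each is assigned 1:1 from a computer-generated list held in sequentially numbered, sealed, opaque envelopes prepared by a person who does not recruit.

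If the semi-experimental design is kept:

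- assign consecutive patients by a fixed rule that the recruiter cannot influence, for example by calendar period;
- adjust the group comparison for the characteristics already listed under Sampling;
- word the conclusion as an association.

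**Cost.** One paragraph changes, and the calculation of 37 per group is unaffected. Someone other than the recruiter has to prepare the list and envelopes, a role the protocol does not now describe. With randomisation the semi-experimental label has to change, and patients in the same department may share the media. Asking them not to would help but would not rule it out. Assignment by period reduces sharing but ties the groups to calendar time, which is one more reason for the cautious conclusion.

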**Inclusion criteria**

1. Patients who do not have movement disorder.

2. Patients who do not have hearing or vision impairment.

3. Patients who do not have a medical history of suffering from cognitive diseases and depression.

4. Patients who do not take neuroleptics.

5. Patients who have not recently experienced a new crisis such as the death of loved ones, hospitalization, etc.

6. Have access to virtual space and educational videos.

**Exclusion criteria**

Patients who experience a new crisis during the research.

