**After colonoscopy**

11) After the operation, did one of the colonoscopy unit staff explain what happened?

Yes, No

12) When you left the colonoscopy unit, were you aware of the results?

Yes, No

13) Did you feel ready to be discharged when you left the hospital?

Yes, No

14) How satisfied were you with your experience when you left the hospital?

Not At All, Low, Moderate, Completely Satisfied, Very Satisfied

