**Discharge time from the hospital**

15) Did you have any complications as a result of your colonoscopy?

Yes, No

16) Would you recommend this hospital to others for colonoscopy?

Yes, No

1. :

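### The only exclusion criterion removes patients after group entry for an undefined new crisis, so patients with a procedure-related complication can be dropped from the satisfaction outcome

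*Protocol*

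**What the plan says.** The Protocol's Exclusion criteria section has a single entry: "Patients who experience a new crisis during the research". It does not define the term. The only explanation is item 5 of the Inclusion criteria: "Patients who have not recently experienced a new crisis such as the death of loved ones, hospitalization, etc". Hospitalization is thus a named example of a crisis, and the list is left open.

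The outcome, according to Research Method, is satisfaction: "the dependent variable (satisfaction of patients undergoing colonoscopy) will be investigated". Appendix No. 2 measures it with questions that run up to discharge. Item 13 asks about readiness for discharge, item 14 asks "How satisfied were you with your experience when you left the hospital", item 15 asks "Did you have any complications as a result of your colonoscopy", and item 16 asks whether the patient would recommend the hospital.

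On how groups are formed, Sampling says that "the participants will be selected purposefully in two control and intervention groups". The Protocol describes no randomisation and no blinding. It does not say who decides that a crisis has occurred, or whether an excluded patient's questionnaire is kept.

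**The concern.** A criterion that acts before entry defines the population. One that acts after entry selects within the groups, and here the selecting event can be part of what is measured. A complication that leads to admission or a longer stay fits the named example of hospitalization. It is also an experience that items 13 to 16 are meant to capture. If these patients are removed, satisfaction is described only for those whose procedure went well enough.

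Two consequences follow, of different strength. First, if the removed patients are less satisfied, the mean is overstated in each group that loses some. Second, the comparison between groups is distorted if removals are more frequent in one group, or are of a different kind. Patient education could plausibly change either, and an undefined criterion leaves room for uneven application.

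**Working it through.** **1. The passages side by side.** The exclusion criterion and inclusion criterion 5 use the same term in adjacent sections, so the gloss in the second is the natural guide to the first. Nothing in either section separates unrelated life events from events caused by the procedure. Read as written, admission for a complication qualifies.

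**2. The plan's own figure.** Inputs from Adult sample size: two-sided alpha 0.05 (z = 1.96), power 0.90 (z = 1.28), standardised effect 0.75.

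n = 2 × (1.96 + 1.28)² / 0.75² = 37.3 per group

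This agrees with the stated 37. The point does not depend on this figure. It supplies the 0.75 SD scale for what follows.

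**3. Effect of removal on one group's mean.** Assumption, not in the Protocol: excluded patients score on average 1 SD below those retained. Let p be the fraction excluded and R the retained mean, in SD units.

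Full mean = (1 − p) × R + p × (R − 1) = R − p

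The retained mean therefore exceeds the full mean by p SD.

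**4. Effect on the difference.** The shift is the gap between the two exclusion rates. The Protocol gives no rates, so a range is shown:

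| Excluded, control | Excluded, media | Shift in difference | True 0.75 SD appears as |
|---|---|---|---|
| equal | equal | 0 | 0.75 |
| 3% | 1% | 0.03 − 0.01 = 0.02 SD | 0.73 |
| 15% | 5% | 0.15 − 0.05 = 0.10 SD | 0.65 |
| 5% | 15% | 0.10 SD the other way | 0.85 |

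**5. Power in the large-gap case.** Removing 15% and 5% from 50 per group leaves 50 × 0.85 = 42.5 and 50 × 0.95 = 47.5, so about 42 and 47. Two-sided t-test power with those numbers is 0.94 at 0.75 SD and 0.86 at 0.65 SD.

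**6. A harsher illustration.** Suppose the excluded patients are exactly the lowest scorers, in one group only, with normal scores and no true effect. Removing the lowest 2%, 5% or 10% raises that group's mean by 0.05, 0.11 or 0.20 SD. Two-sided type I error at 50 per group becomes about 0.06, 0.09 or 0.18. This is an extreme pattern and is not a forecast.

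**The case against.** The strongest reply is that the criterion is meant for unrelated life stress. Its examples sit beside depression and cognitive illness and describe events before entry. The questionnaire is framed around leaving the unit and the hospital, so if it is completed then, only events up to discharge could remove a patient first, and these may be rare. Selection into the groups is in any case the larger source of bias. All of this is fair. It limits the size of the problem but does not remove it, because the text exempts no procedure-related event and does not state when the questionnaire is completed.

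Some stronger readings are tempting but not supported:

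- *The person judging a crisis knows the group.* The Protocol is silent on this. Knowledge of the group is not ruled out, but it is not stated.
- *The exclusion necessarily invalidates the comparison.* With equal rates and similar kinds of exclusion, the calculation above gives no shift in the difference.
- *Bad news from the colonoscopy counts as a crisis.* That rests only on the open end of the list. Item 12 asks whether patients knew their results, not what the results were.
- *Power falls from 89% to 79%.* Those values belong to 37 per group. Excluding 15% and 5% of 50 leaves about 42 and 47, and the fall is from 0.94 to 0.86.
- *Criterion 5 contradicts the rest of the plan.* Sampling states that "background and cause of hospitalization will be statistically investigated", and the Appendix No. 1 questionnaire records reason for admission and length of stay. These are naturally read as the current admission, and criterion 5 as an earlier event. This is an ambiguity to clear up, not a contradiction.

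It can also be said that analysis sets belong in a statistical analysis plan. That holds for much of the detail, but the exclusion criterion itself is fixed in the Protocol, and the fault lies there.

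**Conclusion.** The point stands in a limited form. As written, the plan allows patients to be removed after group entry for an event that may result from the colonoscopy and that bears directly on the outcome. Satisfaction is then overstated in each group that loses such patients, provided they are less satisfied than the rest. The difference between groups is biased only if exclusions differ in rate or kind. The Protocol does not guard against that, since it describes no randomisation, no blinding and no rule for judging a crisis.

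The size cannot be determined from the Protocol. Under the assumed 1 SD deficit it ranges from 0 with equal exclusion, through 0.02 SD, to 0.10 SD for a gap of ten percentage points, in either direction. With few events before discharge it would be negligible. The case for changing the text rests on the low cost of doing so, not on a demonstrated large bias.

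**What to change.** Apply the crisis criterion only before group entry. After that, keep every entered patient who returns a questionnaire in the main analysis, in their own group. Record each crisis by group with its reason, including whether it followed from the procedure, and exclude those patients only in a sensitivity analysis. Also state that inclusion criterion 5 does not refer to the index admission, if that is what is meant.

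The cost is a few sentences in the Protocol and slightly more variable data in the main analysis. No extra patients or visits are needed. The change does not address how patients are selected into the two groups, which is a separate matter.
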